#### Recruitment {15}

The research will be widely disclosed using social media, local TV, radio stations, and announcements in health units near the research site. We will also have an arrangement with the Hospital de Trauma Senador Humberto Lucena for patient referral. Thus, this study will recruit patients with burn wounds residing in the State of Paraíba, who contacted researchers or were referred by the Burn Service of the Hospital de Trauma Senador Humberto Lucena, basic health units, or emergency care units of the city of João Pessoa (Paraíba, Brazil).

### Assignment of interventions: allocation

#### Sequence generation {16a}

The online software randomization.com will be used to allocate participants by blocks into three parallel groups (1:1:1) of 13 subjects: RLG, which will receive photobiomodulation using red LED; ILG, which will receive photobiomodulation using infrared LED; and SG, which will undergo a simulated application of LED therapy.

#### Concealment mechanism {16b}

The researcher responsible for randomization will forward sequentially numbered, opaque, and sealed envelopes to the therapist.

#### Implementation {16c}

Participants and assessors will be blind to allocation, which will be performed by an external researcher not directly involved with participants. The therapist will open the envelope containing the treatment for each participant before the session.

#### Assignment of interventions: blinding

##### Who will be blinded? {17a}

Participants, assessors, and data analysts will be blinded to treatment allocation. After assessments, assessors will fill in a questionnaire indicating which group the participant was allocated. Follow-up appointments will be scheduled to avoid overlap and communication among participants.

##### Procedure for unblinding if needed {17b}

Emergency unblinding will be allowed in case of withdrawal from the trial. Otherwise, to maintain the overall quality and legitimacy, the unblinding will occur exceptionally if the information is essential for further patient management.

### Data collection and management

#### Plans for assessment and collection of outcomes {18a}

Data will be collected using an evaluation form and the following tools: photographic and thermographic images, VAS, Itch Severity Scale, adheremeter, and Vancouver Scale. All standardized instruments used in the study procedure are described in the “Outcomes {12}” section.

#### Plans to promote participant retention and complete follow-up {18b}

Participants can leave the study at any time and without explanation. However, we will extensively inform them about the study setup and requirements during recruitment, highlighting the importance of a complete follow-up. During the study, participants will receive a phone call to remind and engage them before every consultation. In the follow-up period, researchers will verify responses and, if needed, contact participants to complete the follow-up (see the “Attrition and Adherence {11c}” section).

#### Data management {19}

Recruitment, randomization, and blind allocation will be conducted by a researcher who will not participate in other study stages. Experienced assessors will be responsible for recording data, while the project coordinator will be responsible for data management. Data will be collected in a printed form, exported to a digital spreadsheet (Excel®) with double typing and data validation, and stored in a file on the internet (cloud storage) by the project coordinator. Therapists will not have access to data.

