### Who will take informed consent? {26a}

All participants will be informed about the evaluation and treatment procedures during the first interview, which will occur after referral to the laboratory and before randomization. They must sign two versions of the informed consent form to participate (one copy will remain with the participant), following Resolution 466/12 of the National Health Council and the Declaration of Helsinki.

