## Discussion

This study protocol is the first to compare the re-epithelialization rate of second-degree burns, pain, pruritus, skin temperature, quality of wound healing, and scar mobility among participants undergoing photobiomodulation using red and infrared LED. According to the randomization performed before recruitment, thirty-nine participants with burn wounds will be divided into three groups. The following variables will be assessed post-treatment and in the short term: re-epithelialization rate, skin temperature, pain intensity, pruritus intensity, and scar mobility and quality.

Changes in medication prescribed to participants will not be encouraged for ethical reasons, especially medication administered on demand to control symptoms. Both groups will be encouraged to perform standard care for their wounds.

Despite different therapeutic doses, a systematic review indicated that photobiomodulation improved burn healing in animals [23]. Furthermore, only one crossover clinical trial about the topic was published and presented methodological problems, such as the absence of blinding of therapist and participants [15, 16].

Regardless of wound type, the various parameters used in previous studies and clinical trials [24] hinder the recommendation of ideal doses and treatment procedures to heal burns. Because evidence is insufficient, the World Association for Photobiomodulation Therapy does not recommend treatment procedures and optimal doses.

Our study is a randomized controlled clinical trial with minimal risk of bias and intends to identify the type and doses of photobiomodulation that will improve the healing of burn wounds. Positive results will allow the recommendation and implementation of the technique in treatment protocols for these individuals.

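### The protocol contradicts itself on whether the person who allocates also recruits; on one of the two readings the recruiter can know the next arm

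*Protocol article*

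**What the plan says.** The protocol article describes these roles in several places.

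- Data management {19}: "Recruitment, randomization, and blind allocation will be conducted by a researcher who will not participate in other study stages".
- Implementation {16c}: "Participants and assessors will be blind to allocation, which will be performed by an external researcher not directly involved with participants". It adds: "The therapist will open the envelope containing the treatment for each participant before the session".
- Concealment mechanism {16b}: "The researcher responsible for randomization will forward sequentially numbered, opaque, and sealed envelopes to the therapist".
- Sequence generation {16a}: "The online software randomization.com will be used to allocate participants by blocks into three parallel groups (1:1:1) of 13 subjects". It does not name who generates the list.
- Discussion: "According to the randomization performed before recruitment, thirty-nine participants with burn wounds will be divided into three groups".
- Who will take informed consent? {26a} places the first interview, at which participants are informed and consent is sought, at a time "which will occur after referral to the laboratory and before randomization".

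Three further sections matter. Who will be blinded? {17a} lists participants, assessors and data analysts, and no recruiter. Methods for additional analyses {20b} plans no subgroup or adjusted analyses. Trial status says that the study has started and that participants are being enrolled.

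**The concern.** Concealment of allocation requires that whoever decides whether and when a person enters the trial cannot foresee that person's arm. The Data management sentence puts recruitment and randomization in the same hands, while the Implementation section keeps the allocator away from participants. A reader cannot tell which arrangement is in force.

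If it is the first, a recruiter could, knowingly or not, let the next arm influence who is enrolled or when. Burns in this trial differ in prognosis: the Background gives a healing range of 7 to 21 days depending on depth, age and other factors, and the eligibility criteria set no limits on size or on depth within second degree. With 13 participants per arm, a few steered enrolments could unbalance the groups. Blinding of participants, assessors and analysts acts after enrolment and does not protect against this.

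**Working it through.** The plan gives no figure on this point, so the check sets the sections side by side and then asks how much of the sequence each role could foresee.

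**Step 1. Do the two role descriptions agree?** Data management gives one researcher three tasks: recruitment, randomization and allocation. Implementation gives allocation to an outside researcher without direct involvement with participants. Plans to promote participant retention {18b} says that people are informed about the study in the course of recruitment, so recruitment includes contact with them. The same person cannot both recruit and have no direct involvement. The sections conflict.

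**Step 2. What follows if Data management is taken literally?**
- By Concealment mechanism, whoever is responsible for randomization supplies the envelopes. Under Data management that is also the recruiter.
- By the Discussion, randomization precedes recruitment, so the sequence exists while participants are being enrolled.
- The envelopes go to the therapist, who opens them. They conceal the sequence from people who do not know their contents, not from the person who supplied them.

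On this reading the recruiter can know the next arm at enrolment.

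**Step 3. What follows if Implementation is taken literally?** The allocator has no direct contact with participants and someone else enrols. The envelopes then do their job, provided that the person enrolling has no access to the list.

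**Step 4. How much could be foreseen?** Inputs: 39 participants, three arms, 1:1:1, blocked (Sequence generation; Sample size {14}). The article does not state the block size; 3 and 6 are assumptions used to show a range.

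- Chance alone: 1/3 = 33% correct.
- Holding the list: 39/39 = 100% correct.
- No list, but past assignments and block size known, blocks of 3: the best guess is right with probability 1/3, 1/2 and 1 at the three positions. The average is (1/3 + 1/2 + 1)/3 = 61%. The last position is certain, so 1/3 = 33% of assignments are known.
- The same, blocks of 6: the probabilities are 1/3, 2/5, 1/2, 8/15, 3/5 and 1, which sum to 3.367, and 3.367/6 = 56%. The last position is always certain and the fifth is certain with probability 1/5, so (1/5 + 1)/6 = 20% are known.

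The averages are over complete blocks; 39 is 13 blocks of 3 but not a whole number of blocks of 6. These are proportions of assignments that could be foreseen, not estimates of bias.

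**Step 5. Would the planned analysis absorb an imbalance?** Only in part. The pre-treatment assessment is one of the three time points in the mixed model, so baseline is not ignored for repeatedly measured outcomes. Days to complete healing has no pre-treatment value, and no adjustment for burn size or depth is planned.

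**The case against.** The strongest reply is that the two sections devoted to allocation describe a sound design, with sealed numbered envelopes and an allocator kept apart from participants. The conflicting sentence is a summary line under Data management and may simply be loose drafting. This has force. A reader might infer from that line that allocation in this trial is not concealed. The document does not support so firm a conclusion, because Implementation says the opposite.

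Two links in the stronger reading are also inferred. That this researcher generates the list is a natural reading of the word randomization, but Sequence generation names only the software. That this researcher judges eligibility or takes consent is stated nowhere. Recruitment {15} describes publicity and a referral arrangement, Study setting {9} places the eligibility interview in the laboratory without saying who conducts it, and the Data management sentence itself keeps this researcher out of other stages.

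A list made before recruitment is normal practice and no fault in itself. It is also compatible with consent before randomization, if that means before the individual is assigned.

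The contradiction survives all of this. Keeping the researcher out of later stages limits bias in treatment and assessment, but selection bias arises at enrolment, which is the task the sentence assigns. Nor is this detail that a condensed article leaves to a fuller document: the article states the roles, in two incompatible ways.

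**Conclusion.** The point holds as an internal contradiction on a matter that decides whether allocation is concealed. Under Data management, read with Concealment mechanism and the Discussion, the recruiter could foresee up to 39 of 39 assignments. Under Implementation, someone else enrols and the envelopes can work. The first result assumes that the person responsible for randomization knows the sequence and that recruiting gives some influence over who enters or when. Both are reasonable readings, but neither is spelled out.

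A reader might want to express the possible bias in days of healing. The document gives no expected benefit in days and no basis for how many enrolments might be affected, so no such figure is offered. What can be said is that selection bias is possible on one reading, that 13 per arm leaves little room for it, and that the planned analyses would not reliably correct it. No sample size or power figure changes.

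**What to change.** Amend Data management {19} to agree with Concealment mechanism {16b} and Implementation {16c}:

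- The external researcher who holds the list and prepares the envelopes has no part in recruitment, consent or eligibility decisions.
- An existing team member without access to the list recruits and enrols. Given the blocks, it is better that this person does not see past assignments either.
- Each envelope is opened only after consent, eligibility and baseline assessment have been recorded for that participant.

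Because Trial status says that enrolment is under way, also document, and report with the results, who has held the list and who has enrolled participants so far. If these were the same person, new wording cannot undo it, and it should be reported as a limitation.

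The cost is a few sentences of text, at most the reassignment of one task within the existing team, and a short record of past practice. Outcomes and interventions are untouched.

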#### Confidentiality {27}

All information obtained will be stored by the project coordinator at the Federal University of Paraíba. Individual trial identification numbers will be given to participants to ensure privacy regarding identity and data involved in the study. Researchers will also attest that the results obtained will be disclosed exclusively for academic purposes. Names of participants will only be recorded on the informed consent form, which will be kept untraceable in a locked cupboard with the project coordinator and separated from digital data. An anonymous database may be available in the future for collaborative research and prospective meta-analyses. Requests must be authorized by the principal investigator and human research ethics committees.

#### Plans for collection, laboratory evaluation, and storage of biological specimens for genetic or molecular analysis in this trial/future use {33}

Not applicable because no samples will be collected.

## Statistical methods

### Statistical methods for primary and secondary outcomes {20a}

Outcome variables will be re-epithelialization rate, presence and intensity of pain and pruritus, local skin temperature, and scar mobility and quality. Groups will be considered independent variables. Statistical analysis will be performed according to intention-to-treat principles. Descriptive analyses and histogram inspections will determine data normality. Between-group differences and 95% confidence intervals (95% CI) will be calculated using linear mixed models and group, time, and group-versus-time interaction terms. A first-order autoregressive covariance matrix will be considered. Group and time will be considered fixed factors, and participants the random factors. A Q-Q plot will be performed for all variables to consistently and similarly confirm the normality of residues between groups. The SPSS software version 20.0 (IBM SPSS Corp., Armonk, NY) will be used for data analysis.

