### Study objectives

#### Primary objective

The primary objective is to determine whether LED photobiomodulation is superior to simulation to increase the re-epithelialization rate and decrease the healing time of burn wounds.

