#### Primary outcome measures

##### Re-epithelialization rate

The percentage of healed skin tissue (re-epithelialization rate) and the number of days between the start of treatment and total healing process will be assessed using digital images of the burned region. These images will be captured daily from before treatment to follow-up of the re-epithelialization process. A digital camera (Sony Cyber-Shot Dsc-W800, 20.1 megapixels, Brazil) will be positioned on a tripod, parallel to the ground and perpendicularly fixed at a distance of 30 cm from the area to be treated. If the participant cannot stand, images will be captured on a stretcher assuring the same distance and a 90° angle between the area and the camera. The photograph will be captured on a white background with indirect artificial lighting.

Re-epithelialization rate will be assessed by counting the days until complete healing and monitoring the wound area during protocols (ImageJ® software, version 1.36 b). The crust area on the wound edge will be measured using digital image analysis, according to Gabison et al. [19]. The software converts the selected area to cm^2^ by associating the known dimension of the photographed object, area of interest, and the respective number of pixels. Healing will be assessed using a glossary of healing evolution based on the pressure ulcer assessment scale proposed by Bates-Jensen, Vredevoe, and Brecht [20].

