##### Scar mobility in the burned area 

After complete healing, an adheremeter will be positioned (without direct contact) in the central point of the scar most adhered to the skin. The skin will be stretched by centrifugation in four orthogonal directions (caudal, rostral, right, and left sides). Maximum distension will be read on the instrument after each traction. After releasing the tension, the researcher will observe if the landmark will return to the starting point; if not, the measurement will be repeated. This procedure will also be performed at the same location on the contralateral limb [22].

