**Fig. 2 Fig2:**
[figure not shown]
Participant timeline

Sociodemographic data, characteristics of the burn (i.e., type of accident, causal agent, and percentage of body surface affected), when the burn happened, and pharmacological treatment received will be registered on an evaluation form. Participants will be instructed to maintain standard care. A trained researcher will assess and perform therapeutic procedures five times a week, once daily. Wound healing rate, pain, pruritus, skin temperature, mobility restriction, and scar quality will be analyzed.

Digital images of the burned area, skin temperature (infrared image), and pain and pruritus will be assessed daily before therapeutic procedures. Only three assessments will be analyzed: initial (before treatment), final (when re-epithelialization of the burn is complete), and one assessment between initial and final assessments (median time of treatment between initial and final assessment). After treatment and total wound closure, mobility and scar quality will be assessed using the adheremeter and Vancouver Scale, respectively.

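### Days to complete healing, half of the primary objective, is not named in the analysis section, and the only stated model cannot be fitted to it

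*Protocol article*

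**What the plan says.** The Primary objective section asks whether LED photobiomodulation is "superior to simulation to increase the re-epithelialization rate and decrease the healing time of burn wounds". Under the primary outcome (Outcomes {12}, Re-epithelialization rate), the protocol defines the percentage of healed tissue and adds that "the number of days between the start of treatment and total healing process will be assessed using digital images of the burned region". The same section then places both quantities under one label: "Re-epithelialization rate will be assessed by counting the days until complete healing and monitoring the wound area during protocols".

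Statistical methods {20a} lists what will be analysed: "Outcome variables will be re-epithelialization rate, presence and intensity of pain and pruritus, local skin temperature, and scar mobility and quality". Between-group differences are to be "calculated using linear mixed models and group, time, and group-versus-time interaction terms", with a first-order autoregressive covariance and participants as the random factor. No other between-group method is given, and the abstract also names only mixed linear models.

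The text under Participant timeline {13} limits the analysis to three assessments: the initial one, the one at complete closure, and one midway between them. It also states: "After treatment and total wound closure, mobility and scar quality will be assessed using the adheremeter and Vancouver Scale, respectively". Section {20c} relies on the mixed model to deal with missing data under intention to treat.

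**The concern.** Days to healing is one number per participant. A model built on time, a group-by-time interaction and serial correlation has nothing to work on there. If the repeated area measure answered the same question, the gap would be small. But the analysed assessments are anchored to each participant's own closure, so that measure says little about speed.

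What is at stake is half of the primary question. Its analysis would have to be chosen later. The obvious improvised choice, comparing mean days among those seen to heal, would drop everyone who leaves before closure from an analysis that the protocol describes as intention to treat.

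**Working it through.** **1. The plan's own sample size.** Inputs from Sample size {14}: effect size 0.5 (read as Cohen's f), 80% power, alpha 0.05, three groups, repeated measures ANOVA, N = 30. The number of measurements m and their correlation rho are not stated. I take m = 3 from the timeline and assume rho = 0.5. For the between-groups test, lambda = f²·N·m / (1 + (m − 1)·rho), with 2 and N − 3 degrees of freedom:

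- lambda = 0.25 × 30 × 3 / 2 = 11.25, power 81.7%. The smallest N in equal groups is 30, as stated.
- With m = 3, rho = 0.3 gives 24 and rho = 0.7 gives 36. Two other pairs also give 30: m = 2 with rho = 0.3, and m = 4 with rho = 0.5. All of these rest on repeated measurement.

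For an outcome with one value per participant, lambda = f²·N:

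| N | lambda | power |
|---|---|---|
| 30 | 7.5 | 63.5% |
| 39 | 9.75 | 76.9% |

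Reaching 80% takes 42 participants. The stated size therefore does not carry over to a single day count at the same f.

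**2. Can the stated model be fitted?** With three groups and three times, the fixed part has 1 intercept + 2 group + 2 time + 4 interaction = 9 parameters.

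- Three records per participant: the design matrix has rank 9, so all are estimable.
- One record per participant: rank 3, so only the three group means are estimable. Time and the interaction drop out. Neither an autoregressive correlation nor a participant variance separate from the residual can be identified.

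This holds for days to healing and for the two scar measures, each taken on one occasion. The adheremeter's four directions and its contralateral reading are repeats in space, not in time.

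**3. Does the repeated area measure recover speed?** At the final analysed assessment every healed participant is fully re-epithelialized by definition. On the natural reading, the midpoint is set by the participant's own treatment duration. As an illustration, take the two ends of the healing range in the Background, 7 and 21 days, and assume that closure is proportional to elapsed time:

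| Healed on | Initial | Midpoint | Final |
|---|---|---|---|
| Day 7 | 0% | 50% (day 3.5) | 100% |
| Day 21 | 0% | 50% (day 10.5) | 100% |

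A threefold difference in healing time leaves no difference in the analysed percentages. The same follows whenever the healed fraction depends only on elapsed time divided by the participant's own healing time. Differences in the shape of the closure curve can still show; differences in speed largely cannot.

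**4. Missing values.** A mixed model can use the records that a participant does have. With a single outcome value, a participant who leaves before closure has none, so the provision in {20c} does nothing for this outcome.

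**5. What a time-to-event analysis could detect.** This takes one LED arm against sham, assuming that everyone heals, with D the number of closures. Schoenfeld's approximation gives the hazard ratio for 80% power as exp[(1.960 + 0.842) / √(D/4)]:

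- D = 20 (10 per arm): exp(2.802 / 2.236) = 3.5.
- D = 26 (13 per arm): exp(2.802 / 2.550) = 3.0.

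At an assumed hazard ratio of 2, power is Φ(√(D/4) × 0.693 − 1.960), which is 34% for D = 20 and 42% for D = 26. For 80% power, 4 × 2.802² / 0.693² = 65.3, so 66 closures would be needed.

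**The case against.** The best reply is that healing time is not really absent. The outcome section has one primary heading and counts days under it, the analysis section lists that heading, and Sample size {14} and Interim analyses {21b} both speak of one primary outcome or endpoint. That stands as far as it goes: the fair charge is one blurred endpoint with two components, not an outright omission. It supplies no analysis, because the day count is still one value per participant.

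A second reply is that dropping the time terms leaves an ordinary group comparison, and that an analysis plan would normally settle this. For the scar outcomes, which are secondary, this largely stands, and a clarifying clause is enough. For healing time it does not. A single model is stated for all outcomes, it fails for this one, and the choice of assessments prevents the area measure from standing in.

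Three stronger readings are tempting but unsupported:

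- **Inflated error across four primary tests** (two LED arms, two outcomes). The protocol never states four separate tests or a rule that success on any one suffices.
- **About 4 of 13 per arm lost, the slowest healers among them.** The 30% in Sample size {14} is a planning allowance. Treatment continues until closure with no cap on sessions, so missing day counts arise only from withdrawal, exclusion or attrition, and how these relate to healing is unknown.
- **The contralateral adheremeter reading must enter a model.** The protocol says "This procedure will also be performed at the same location on the contralateral limb" and gives the reading no analytic role, but how it is used can be left to an analysis plan.

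**Conclusion.** The point holds. Half of the primary objective has no analysis that can be carried out as written, and the repeated area analysis largely removes the feature, speed, that this half is about. The size of the problem is structural: three of nine fixed-effect parameters are estimable for a single-value outcome, and power at f = 0.5 is 63.5% to 76.9% for 30 to 39 participants instead of the intended 80%.

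The non-fit of the model needs no assumption. The loss of speed rests on reading the midpoint as each participant's own. The power figures rest on f = 0.5 from the protocol; the rho of 0.5 used to reproduce N = 30 and the hazard ratio of 2 are assumptions. No direction or amount of bias from dropout can be claimed. What can be said is that anyone without observed closure would contribute nothing to a comparison of day counts, contrary to the stated intention to treat.

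**What to change.** In Statistical methods {20a}:

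1. Name time from start of treatment to complete re-epithelialization as a separate outcome, and state whether it or the percentage of area healed is the primary one. The interim analysis, which is defined on the primary endpoint, needs the same answer.
2. Analyse it as time to event: Kaplan-Meier curves with a log-rank test or Cox model, with participants without observed closure censored at their last image.
3. Add a sensitivity analysis for that censoring. If dropout is related to healing, for example through infection or a worsening wound, censoring at the last image is itself biased.
4. State that scar mobility and Vancouver score are compared between groups without time terms.

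The cost is mainly wording and standard procedures: the images are already taken daily before each session, so no new data are required. The change should go through the amendment and registry route in {25}, before those deciding have seen outcomes by arm. The real downside is power, since 13 per arm supports only large pairwise effects on healing time, and the protocol should say so. Adjustment for covariates such as initial wound area is optional. It would also require amending {20b}, which rules out adjusted analyses.
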